#### Strategies to improve adherence to interventions {11c}

Every participant has a fixed investigator for assessments at baseline and follow-up, and the investigator will keep in touch with the participant to provide encouragement and remind the patients of taking medicine.

#### Relevant concomitant care permitted or prohibited during the trial {11d}

Benzodiazepines and similar hypnotics are allowed for short-term use with careful records.

#### Provisions for post-trial care {30}

There is no anticipated harm and compensation for trial participation.

### Outcomes {12}

The following is the primary outcome:Clinical remission (examiner-rating), defined as total scores less than or equal to 7 on the HAMD-24 at the end of the 12th week

The following are the secondary outcomes:Clinical remission (self-rating), defined as total scores less than or equal to 5 on the QIDS-SR16 at the end of the 12th weekEarly improvement, defined as a ≥ 20% decrease from the baseline HAMD-24 at the end of the 2nd weekTreatment response, defined as a ≥ 50% decrease from the baseline HAMD-24 at the end of the 12th weekSeverity and incidence of adverse eventsThe time of treatment discontinuation for any causeWorking or learning time lost to any cause associated with the present study

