## Introduction

### Background and rationale {6a}

Currently, there are about 340 million people with major depressive disorder (MDD) worldwide, and the lifetime prevalence rate of MDD is 3.9% in China [1]. The World Health Organization has reported that MDD would become the most serious global burden of disease and eventually turn into a public health problem in 2030 [2].

Depression is clinically heterogeneous, and based on the criteria of the Diagnostic and Statistical Manual of Mental Disorders, Fifth Edition (DSM-5), depressive disorders could be specified with eight kinds of clinical features. Atypical features were incorporated into the DSM-5 as an illness specifier, including mood reactivity, weight gain or appetite increase, hypersomnia, leaden paralysis, and interpersonal rejection sensitivity. MDD with atypical features, namely depression with atypical features (AFD), is one of the most common clinical specifiers of MDD accounting for 15~36% [3]. Rather than a classification of diseases, AFD is a distinctive group of MDD, regarded as a potential indicator for predicting bipolar disorder (BD) or even a variant of BD-II [4–6]. Through our BIPAS survey and review of the literature [7, 8], we found that there is still a lack of evidence from high-quality studies to enhance the clinical guidelines for the diagnosis, treatment, and prognosis of AFD.

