### Data collection and management

#### Plans for assessment and collection of outcomes {18a}

M.I.N.I International Neuropsychiatric Interview (MINI) [19] is used to conduct a comprehensive screening. HAMD-24 and Quick Inventory of Depressive Symptomatology (self-report) with 16 items (QIDS-SR16) [20] are applied to evaluate depressive symptoms, Hamilton’s Anxiety Scale (HAMA) [21] is used to assess anxious symptoms, HCL-32 is performed to recognize mania or hypomania symptoms, and Quality of Life Scale with 6 items (QOL-6) [22] is used to evaluate the life quality briefly. Additionally, family history, physical or mental comorbidity, the medication used before, prescription for this time, number of episodes, first-onset time and age, and duration of illness are also questioned and recorded. Adverse events are recorded in adverse events report (AER) forms when needed during the follow-up period. Cognitive function is assessed using the MATRICS Consensus Cognitive Battery (MCCB) [23]. MCCB consists of 10 subtests that mainly reflect the cognitive function of 7 cognitive domains including speed of processing, attention and vigilance, working memory, verbal learning, visual learning, reasoning and problem-solving, and social cognition.

After the 12-week randomized intervention, patients with AFD will be followed up until switching to BD for a maximum of 4 years. Face-to-face interviews, including clinical and neurocognitive assessments, MRI scans, and blood specimen collection, will be scheduled for 12 weeks, 1 year, and 4 years. The interim interviews of clinical assessments will be performed at 2 weeks, 4 weeks, 8 weeks, 6 months, 2 years, and 3 years through offline or online approaches. Patients with AFD will undergo a semi-structured interview at the follow-up time points to determine whether they have experienced mania or hypomania or have been diagnosed with bipolar disorder by psychiatrists during the interval since the previous follow-up. If a patient has experienced mania or hypomania or has been diagnosed with bipolar disorder by psychiatrists during the interval, multidimensional data will be recollected and follow-up will be terminated.

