## Statistical methods

### Statistical methods for primary and secondary outcomes {20a}

To evaluate the effectiveness of the 12-week treatment for patients with AFD, we plan to perform an intention-to-treat analysis to pursue our primary outcome. A mixed-effect model for repeated measures will be applied to analyze the main effects of interventions, time, and the interaction on HAMD total scores to find the optimal treatment for patients with AFD. Covariates like gender, age, education, and the baseline severity of depressive symptoms will be added to the model to correct the potential confounding effects.

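### Remission and response rest on depression scores alone, and no named 12-week outcome compares mania or hypomania between the randomised arms

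*Protocol article*

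**What the plan says.** The Outcomes section {12} gives the primary outcome as "Clinical remission (examiner-rating), defined as total scores less than or equal to 7 on the HAMD-24 at the end of the 12th week". The secondary efficacy outcomes are a QIDS-SR16 threshold, early improvement on the HAMD-24 and response on the HAMD-24. Adverse events (by severity and frequency), all-cause discontinuation time and lost work or study time complete the list. Mania, hypomania and switching are not named.

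The statistical methods section {20a} states: "A mixed-effect model for repeated measures will be applied to analyze the main effects of interventions, time, and the interaction on HAMD total scores", with the purpose "to find the optimal treatment for patients with AFD". Switching is analysed only in section {20b}, as the binary outcome of a prediction model.

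Section {18a} does plan to measure it: "HCL-32 is performed to recognize mania or hypomania symptoms", and "Patients with AFD will undergo a semi-structured interview at the follow-up time points to determine whether they have experienced mania or hypomania". If a switch is found, "multidimensional data will be recollected and follow-up will be terminated". The visit list reads: "The interim interviews of clinical assessments will be performed at 2 weeks, 4 weeks, 8 weeks, 6 months, 2 years, and 3 years", with week 12 among the face-to-face visits.

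The background {6a} describes AFD as "regarded as a potential indicator for predicting bipolar disorder (BD) or even a variant of BD-II". The intervention section {11a} randomises between SSRI/SNRI alone, SSRI/SNRI with a mood stabilizer, SSRI/SNRI with quetiapine, and TAU.

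**The concern.** A HAMD threshold is conventional in unipolar depression. Here the rationale is that the population may not be purely unipolar, and two of the four arms add a mood stabilizer or quetiapine to an antidepressant. Polarity switch is therefore an obvious outcome on which the arms could differ, yet it is absent from the named 12-week comparison.

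The efficacy outcomes look in one direction only. A patient whose depressive symptoms have gone because a hypomanic episode has begun can meet the remission and response definitions and be counted with patients who are well. If such patients are more frequent in one arm, that arm's remission rate is flattered, and no named outcome would show readers why.

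**Working it through.** **1. A switch found at week 12.** A patient is depressed at week 8, becomes hypomanic, and attends at week 12. The HAMD-24 is rated at that visit. If it is 7 or less, the primary definition is met. Because entry requires a score of at least 20, a score of 7 or less is a fall of at least 13/20 = 65%, so response is met too. No rule in {12}, {20a} or {20c} reclassifies this patient. If the score is above 7, the patient is not a remitter, so the problem is confined to low-scoring switchers.

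**2. A switch found at week 2, 4 or 8.** The paragraph in {18a} that holds the switch interview and the end-of-follow-up rule opens with the period after the 12-week intervention, yet its visit list includes weeks 2, 4 and 8. If the rule applies at those visits, the patient has no week-12 score and falls under the multiple imputation of {20c}, which may impute remission. If it does not apply, the observed week-12 score counts as in step 1. Neither route makes the switch a non-remission.

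**3. Size of the effect on remission.** Let p be the switch-free remission rate and s the proportion of the arm that has switched but scores 7 or less.

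Observed difference (add-on minus alone) = (p_add + s_add) − (p_alone + s_alone) = true difference − (s_alone − s_add)

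Each 1-point excess of such patients in one arm moves the difference by 1 point; s_alone = s_add gives no bias. The documents give no value for s. Assume s_alone = 2–8% and s_add = 0–2%:
- smallest shift: 2 − 2 = 0 points
- largest shift: 8 − 0 = 8 points
- at 120 per arm, patients so counted in the SSRI/SNRI-alone arm: 0.02 × 120 = 2.4 to 0.08 × 120 = 9.6

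**4. What this could do to one comparison.** The sample-size section's own steps reproduce: d = 0.5, two-sided 0.05 and 80% power give 63 per group (normal approximation), and 63/0.70 = 90. No stated figure is in dispute; only the planned 120 per arm is used here. Assume switch-free remission of 35% on SSRI/SNRI alone and 50% on an add-on arm, all 120 per arm assessed, and a two-sided 0.05 test of two proportions. Power = Φ[(|d| − 1.96·SE₀)/SE₁], with SE₀ pooled and SE₁ unpooled.

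| Low-scoring switchers, alone vs add-on (assumed) | Observed remission | Difference | Power |
|---|---|---|---|
| 0% vs 0% | 35% vs 50% | 15 points | 65.4% |
| 2% vs 0% | 37% vs 50% | 13 points | 52.9% |
| 5% vs 1% | 40% vs 51% | 11 points | 40.1% |
| 10% vs 2% | 45% vs 52% | 7 points | 19.0% |
| 5% vs 5% | 40% vs 55% | 15 points | 64.5% |

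First row: d = 0.15, SE₀ = √(2 × 0.425 × 0.575/120) = 0.0638, SE₁ = √((0.35 × 0.65 + 0.50 × 0.50)/120) = 0.0631, so (0.15 − 0.1251)/0.0631 = 0.395 and Φ = 0.654. The 10% row lies outside the range in step 3 and is there to show an 8-point excess.

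**The case against.** The strongest reply is that depressive remission is a legitimate efficacy outcome, and that benefit and harm may be reported separately. Adverse events are a secondary outcome and are all to be recorded and graded; HCL-32 and interview data are collected; conversion to BD is the study's third aim; and arm is known for every patient. Prior mania or hypomania and HCL-32 scores of 14 or more are excluded at entry, and the patient in question must both switch and score 7 or less. A condensed article may also leave such handling to the full protocol or SAP.

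Much of this stands. It rules out the inference that the RCT could not show switching at all: the data will exist and could be tabulated by arm. It also weighs against rewriting the primary outcome. That would add a second unblinded clinical judgement to the endpoint of an open-label trial already enrolling, and {18a} describes an interview about the interval since the last visit, not a rating of current state.

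What does not stand is that nothing is missing. The outcome definitions and list are stated in full. Nothing says that a switch is recorded as an adverse event, and such an entry would not stop the patient counting as a remitter. The entry criteria act at baseline only, and the protocol still expects conversions to model.

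**Conclusion.** The point holds as a gap in the named outcomes: a patient found manic or hypomanic at week 12 with a HAMD-24 of 7 or less is a remitter, and no named 12-week outcome compares switching by arm.

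A reader might infer that the remission comparison is biased towards the arms without an add-on. The documents do not support that. They give no switch rate by arm, and the difference is biased only if low-scoring switchers differ between arms. Only the SSRI/SNRI-alone arm is defined without an add-on; TAU permits any drug treatment that follows MDD guidelines and may include one. The 0 to 8 points, and their direction, come from the assumed rates and from counting in s only switchers who score 7 or less.

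The percentage-point arithmetic applies to remission. It does not carry over to the mixed model on HAMD totals, where such a patient simply contributes a low score.

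**What to change.** Keep the primary outcome as it is, and:

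1. In {12}, name mania or hypomania within 12 weeks, by randomised arm, as a secondary safety outcome, using the interview and HCL-32 of {18a}.
2. Add a sensitivity analysis of remission and response in which patients with mania or hypomania by week 12 count as non-remitters and non-responders. Include those whose follow-up ended early for this reason, rather than imputing them under {20c}.
3. In {18a}, state whether the switch interview and the end-of-follow-up rule do or do not cover the week 2 to 12 visits, and reconcile the paragraph's opening with its visit list. The visit schedule in Fig. 2 was not available for this check.

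The cost is small if the interview covers weeks 2 to 12: no new instrument or visit, but an amendment reported as {25} provides. The new outcome will have few events and low precision; at the assumed 5% and 1%, 120 × 0.05 = 6 and 120 × 0.01 = 1.2 expected patients per arm. Remission and response rates will be slightly lower in the sensitivity analysis.

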### Participant timeline {13}

The participant timeline is shown in Fig. 2.

**Fig. 2 Fig2:**
[figure not shown]
Participant timeline MCCB, MATRICS Consensus Cognitive Battery; MRI, magnetic resonance imaging; MINI, M.I.N.I International Neuropsychiatric Interview; HAMD, Hamilton’s Depression Scale with 24 items; QIDS, Quick Inventory of Depressive Symptomatology (self-report) with 16 items; HAMA, Hamilton’s Anxiety Scale; HCL, Hypomania Symptom Checklist-32; QOL, Quality of Life Scale with 6 items; AER, adverse events report; SSRI/SNRI, selective serotonin reuptake inhibitor/serotonin-noradrenaline reuptake inhibitor; TAU, treatment as usual

### Sample size {14}

The sample size estimation refers to the primary outcome. A clinically relevant medium effect size (*d* = 0.5) is expected to be found in a two-sample *t*-test of at least one of the three interventions compared to TAU when calculating the sample size. Using the power of 1−*β* = 80% and the significance level of *α* = 0.05 (two-sided), 63 participants are needed per group. Considering a drop-out rate of ≤ 30%, 90 participants need to be allocated to each group. Finally, we planned to recruit 120 patients per group for a total of 480 included patients with AFD.

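### The sample size is tied to the binary remission outcome but calculated as a t-test at d = 0.5, so 80% power for remission is not shown

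*Protocol article*

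**What the plan says.** Outcomes {12} names a single primary outcome: "Clinical remission (examiner-rating), defined as total scores less than or equal to 7 on the HAMD-24 at the end of the 12th week". Each patient either meets it or does not.

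Sample size {14} opens with "The sample size estimation refers to the primary outcome" and continues: "A clinically relevant medium effect size (*d* = 0.5) is expected to be found in a two-sample *t*-test". The comparison is of "at least one of the three interventions compared to TAU when calculating the sample size". With 80% power and a two-sided 5% level, the section concludes that "63 participants are needed per group". It raises this to 90 for drop-out of up to 30% and then sets recruitment at 120 per group, 480 in all.

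Statistical methods {20a} plans an intention-to-treat analysis directed at the primary outcome, but the model it describes is a repeated-measures mixed model on HAMD total scores. Section {20c} plans multiple imputation for missing data.

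The article gives no remission rate, risk difference or odds ratio for any arm.

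**The concern.** A standardised mean difference and a t-test describe a comparison of means. The named primary outcome is a comparison of proportions, and its power depends on the remission rates in the two arms. Neither rate is stated, so the 80% in section {14} cannot be a property of the remission comparison.

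This is more than a matter of labelling. If d = 0.5 is a shift in the depression score, cutting that score at 7 discards information, and the same number of patients gives less power for remission than for the score. A remission result with no significant difference would then be read against a claimed 80% power that was never worked out for it. As written, a reader cannot tell what difference in remission the trial could detect.

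**Working it through.** **Inputs from the article.** d = 0.5, two-sided alpha 0.05, power 80%, 63 per group, drop-out 30%, 90 per group and 120 planned per group (Sample size {14}); remission defined as HAMD-24 of 7 or less at week 12 (Outcomes {12}).

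**Inputs assumed.** TAU remission of 20–50%, and d = 0.5 read as a shift in the underlying depression score. The article gives neither.

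**Step 1: reproduce the stated figures.** n = 2(1.960 + 0.842)² / 0.5² = 62.8, rounded up to 63 per group. Drop-out: 63 / 0.70 = 90. Both are right for a continuous outcome. The planned 120 leaves 120 × 0.70 = 84 evaluable per arm.

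**Step 2: convert d = 0.5 to remission rates.** Let p0 be the TAU rate and p1 the rate on the better arm.

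- Latent-normal: p1 = Φ(Φ⁻¹(p0) + 0.5). For p0 = 0.30: Φ(−0.524 + 0.5) = 0.490.
- Logistic: odds ratio = exp(0.5π/√3) = 2.48. For p0 = 0.30: odds 0.429 × 2.48 = 1.06, so p1 = 0.515.

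**Step 3: power for two proportions** (pooled variance under the null, no continuity correction, one intervention against TAU):

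power = Φ{ [ |p1 − p0| − 1.96·√(2p̄(1−p̄)/n) ] / √( [p0(1−p0) + p1(1−p1)]/n ) }, where p̄ is the mean of p0 and p1.

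Example, latent-normal, p0 = 0.30, n = 63: (0.190 − 1.96 × 0.0871) / 0.0854 ≈ 0.23, so power is about 59%.

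| TAU remission | Conversion | Better arm | Power, n = 63 | Power, n = 84 | Power, n = 120 | n per arm for 80% |
|---|---|---|---|---|---|---|
| 20% | latent-normal | 36.6% | 54.5% | 67.0% | 82.0% | 115 |
| 30% | latent-normal | 49.0% | 59.0% | 71.7% | 85.9% | 103 |
| 40% | latent-normal | 59.7% | 60.3% | 72.9% | 86.9% | 100 |
| 50% | latent-normal | 69.1% | 59.3% | 71.9% | 86.1% | 102 |
| 20% | logistic | 38.2% | 61.8% | 74.4% | 88.0% | 97 |
| 30% | logistic | 51.5% | 69.4% | 81.5% | 92.8% | 81 |
| 40% | logistic | 62.3% | 71.1% | 83.0% | 93.7% | 78 |
| 50% | logistic | 71.2% | 68.8% | 81.0% | 92.5% | 82 |

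At 63 evaluable per arm no row reaches 80%. At 84, the latent-normal rows all fall short, while the logistic rows pass for TAU rates of 30–50%. At 120 with complete data, every row passes. The assumed range matters: at a TAU rate of 10%, the latent-normal power is 55% with 84 and 70% with 120.

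**Step 4: detectable difference.** With 84 evaluable per arm, 80% power needs a gain of 19.7, 21.1, 21.5 and 21.0 percentage points at TAU rates of 20, 30, 40 and 50%. At 30%, that means about 51% on the better arm.

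**Step 5: the same design on the score.** The t-test at d = 0.5 with 84 per arm has 89.6% power.

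**The case against.** The strongest reply is that the trial being run has 120 per arm, not 63. Section {20a} plans intention-to-treat and section {20c} multiple imputation, so the effective information lies somewhere between 84 and 120 patients per arm. On the latent-normal conversion that spans about 67–87% power, a range that contains 80%; on the logistic conversion it spans about 74–94%. This stands, and it limits the conclusion. It does not settle the matter, because imputation does not recover everything lost to drop-out, so the figures at 120 are an upper bound. The article also never justifies 120 on the remission scale.

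A second reply is that the t-test matches the planned analysis, since section {20a} models HAMD total scores. That is true, and it explains where the calculation came from. It does not make remission a continuous outcome; it shows that Outcomes {12} and Statistical methods {20a} point to different variables.

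A third is that 0.5 might be meant as Cohen's h, for which 63 to 66 per arm would do at TAU rates of 10–60%. The text says d and names a t-test.

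Finally, the article calls the study exploratory, and its first aim is biomarkers. That lowers the urgency, but the section still makes an explicit power claim for a named outcome.

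A reader might infer more: that the trial is underpowered for remission, or that the sample size arithmetic is wrong. The article supports neither. It states no remission rates, so true power cannot be fixed, and 63 and 90 both reproduce. Nor should power be marked down by counting drop-outs as non-remitters: the article sets no such rule and plans imputation instead.

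**Conclusion.** The point holds as a mismatch between the outcome and the method. The 63 per group, and the 90 after drop-out, are valid for a continuous HAMD score only. If TAU remission is 20–50% and d = 0.5 is a shift in the underlying score, 63 evaluable patients per arm do not give 80% power for remission under either conversion. For the planned 120 per arm the conclusion is weaker: whether 80% is reached depends on the TAU rate, the conversion and how much drop-out costs. The article neither shows nor secures 80% for its primary outcome, which is different from establishing that the trial misses it. This should be fixed, but it is not grounds for changing the trial's size.

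**What to change.** Restate Sample size {14} on the remission scale for the planned 120 per arm. Give an assumed TAU remission rate with a range, and the difference detectable with 84 evaluable per arm at 80% power and two-sided 0.05: about 20–22 percentage points, for example 30% to 51%.

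Keep the d = 0.5 t-test but label it as power for the week-12 HAMD-24 score, about 90% with 84 per arm. That matches the mixed model in Statistical methods {20a}. Word {12}, {14} and {20a} so that they agree on which variable is primary and which calculation and analysis belong to it.

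The cost is about a paragraph of text and no extra patients. The downside is that the stated power, or the detectable difference, for remission becomes less favourable than the present wording suggests.

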### Trial design {8}

The iDoT-AFD study is a multicenter, exploratory, prospective, open-label study consisting of a 12-week parallel-group RCT with an allocation ratio of 1:1:1:1 to evaluate the clinical efficacy of four interventions and a prognosis study focusing on conversion to BD with a maximum of 4 years follow-up (Fig. 1).

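### The sample size targets an effect in any one of three arms against TAU but spends the full 0.05 on a single contrast; name the three contrasts as a family and restate the calculation

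*Protocol article*

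**What the plan says.** All references are to the protocol article.

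- **Sample size {14}** refers to the primary outcome and assumes "A clinically relevant medium effect size" (d = 0.5) in a two-sample t-test "of at least one of the three interventions compared to TAU when calculating the sample size". Power is "80% and the significance level of" alpha is 0.05: "0.05 (two-sided), 63 participants are needed per group". Then: "Considering a drop-out rate of ≤ 30%, 90 participants need to be allocated to each group". The paragraph ends: "we planned to recruit 120 patients per group for a total of 480 included patients with AFD". No reason is given for going from 90 to 120.
- **Trial design {8}** describes a "12-week parallel-group RCT with an allocation ratio of 1:1:1:1 to evaluate the clinical efficacy of four interventions" and labels the study exploratory.
- **Outcomes {12}** makes the primary outcome binary: remission, a HAMD-24 total of 7 or less at week 12. No remission rates are given anywhere.
- **Statistical methods {20a}** plans a mixed model for repeated measures on HAMD totals, with treatment, time and their interaction, "to find the optimal treatment for patients with AFD".

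No section divides the 0.05, says which comparisons it covers, or calls it family-wise.

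**The concern.** The hypothesis that sets the size of the trial is a union: an effect in one or more of three arms, each compared with the same TAU arm. The alpha attached to it is the one for a single comparison. The two do not belong together, and the mismatch costs something whichever way the analysis goes.

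- If the three contrasts are each tested at 0.05, as the calculation implies, the chance of at least one false difference exceeds 5%.
- If the analysis adjusts for three contrasts, the stated 63 and 90 per group no longer deliver the stated 80% power.

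The Abstract and Discussion present the results as evidence for clinical guidelines. A reader of a positive contrast with TAU will want to know the error rate behind it.

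**Working it through.** **Inputs from the article.** d = 0.5; power 80% (z = 0.842); two-sided alpha 0.05 (z = 1.960); drop-out 30%; 120 allocated per arm; allocation 1:1:1:1. Equal arms sharing one control give a correlation of 0.5 between any two contrasts with TAU.

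**1. Reproduce the stated figures.** n per arm = 2(z_alpha + z_power)² / d².
- 2(1.960 + 0.842)² / 0.25 = 62.8, so 63. The exact t-test gives 63.8, so 64.
- 63 / 0.70 = 90.

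The stated figures therefore come from the whole 0.05 placed on one contrast.

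**2. Error rate if three contrasts are each tested at 0.05.** With c = 1.960, φ and Φ the standard normal density and distribution function, and u the standardised TAU mean:
- P(at least one false difference) = 1 − ∫ φ(u) [Φ(√2·c + u) − Φ(−√2·c + u)]³ du = 0.125. Simulation gives 0.124–0.125; the Bonferroni bound is 3 × 0.05 = 0.15.
- Counting only false superiority over TAU: 1 − ∫ φ(u) Φ(√2·c + u)³ du = 0.063, against a nominal 0.025.
- If all six pairs were tested at 0.05 (studentized range, four groups): about 0.20.

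**3. Power at 63 evaluable if the three contrasts are corrected.** Power ≈ Φ(d√(n/2) − z_alpha), where 0.5 × √(63/2) = 2.806.
- Bonferroni, alpha 0.05/3 = 0.0167, z = 2.394: Φ(0.412) = 66% (exact t-test 65%).
- Dunnett, critical value 2.349, alpha 0.0188: Φ(0.457) = 68% (exact t-test 66%).

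This is power for one given contrast with a true d of 0.5. If several arms were truly better, the chance of detecting at least one would be higher.

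**4. What a correction needs, against 120 × 0.70 = 84 evaluable per arm.**

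| Family and method | Evaluable n, normal approx. | Allocated (÷ 0.70) | Evaluable n, exact t-test | Allocated | Power at 84, normal / exact t |
|---|---|---|---|---|---|
| Three vs TAU, Dunnett | 82 | 118 | 83 | 119 | 81.4% / 80.6% |
| Three vs TAU, Bonferroni | 84 | 120 | 86 | 123 | 80.1% / 79.3% |
| Six pairs, Tukey | 94 | 135 | 95 | 136 | 74.9% / 73.9% |
| Six pairs, Bonferroni | 97 | 139 | 99 | 142 | 72.6% / 71.5% |

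For example, Bonferroni for three contrasts: 2(2.394 + 0.842)² / 0.25 = 83.8, so 84, and 84 / 0.70 = 120.

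**5. The binary scale.** The article gives no remission rates, so the following pairs are assumptions. At alpha 0.0167 and 80% power, 40% versus 65% needs 83 per arm, 40% versus 60% needs 130, and 40% versus 55% needs 231. With 84 evaluable, power is 81%, 58% and 33% respectively.

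**The case against.** The strongest reply is that the Sample size section states a planning assumption and not a rule for declaring success. The analysis described is a mixed model. An overall test of treatment or of its interaction with time at 0.05 has a 5% error rate when no arm differs, which is the situation behind the 12.5%. The choice of contrasts and adjustment is normally left to an analysis plan, which is not shown. The study is also labelled exploratory, and Objectives {7} places treatment comparison second to biomarkers.

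Much of this stands, and it rules out some tempting readings:

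- **That the trial will run at 12.5% or 20% error.** The article does not say that unadjusted pairwise tests decide the result, and it never claims a 5% family-wise rate. The 12.5% is conditional on testing as sized; the 20% further assumes all six pairs.
- **That 120 per arm covers any correction, or was chosen to cover one.** It covers the three TAU contrasts at d = 0.5, but not all six pairs. The article does not explain 120, so its match with the Bonferroni figure may be coincidence.
- **That a positive finding would be two and a half times as likely to be false.** A type I error rate is not the probability that a positive claim is wrong.

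What does not stand is the suggestion that this is only detail left to the analysis plan. The alpha, the hypothesis and the resulting 63 and 90 are all stated here, and they do not fit each other. An adjustment in an unseen plan would leave those two figures too small. An overall test would not by itself protect later claims about individual arms when some arms differ and others do not.

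**Conclusion.** The point holds as an inconsistency within the sample-size paragraph: a hypothesis about any of three contrasts is sized with the alpha for one. Tested as sized, the chance of at least one false difference from TAU is about 12.5% (false superiority about 6.3% against 2.5%). Corrected, 63 evaluable per arm gives about 65–67% power for a contrast. The planned 120 per arm repairs this for the three TAU contrasts with Dunnett, and to within three patients per arm with Bonferroni by the exact t-test.

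The error rates assume equal arms and a shared TAU group. The headroom further assumes d = 0.5 on a t-test and drop-out no higher than 30%; it is not established for binary remission. Given the exploratory label and the absence of a written success rule, this is a moderate issue and not a must-fix.

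**What to change.** 1. In the statistical methods, name the three active-versus-TAU contrasts of the primary outcome as the family and control it at two-sided 0.05 with Dunnett, or Holm if a simpler procedure is preferred.
2. In Sample size {14}, replace the calculation behind 63 and 90 with one at the adjusted alpha. For Dunnett with d = 0.5 and 30% drop-out, that is about 83 evaluable and 119 allocated per arm, which also supplies a stated basis for the planned 120. If remission remains the primary outcome, state the assumed rates and confirm that 120 is enough on that scale.
3. Label comparisons between active arms, and any naming of a best arm, as secondary, with Tukey-type adjusted intervals, and say that 120 per arm does not give 80% power for all six pairs.

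The cost is a few sentences and a stricter threshold for each contrast (about 0.019 instead of 0.05). With Dunnett at d = 0.5, no patients are added.
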